### Ethical issues

The study plan has been approved by the Ethical committee of the Hospital District of Northern Savo (no. 71/2016). This study is conducted in accordance with the ethical standards laid down in the 1964 Declaration of Helsinki and its later amendments. The participants received both oral and written information about the study, and they gave a written informed consent. They have right to discontinue the study without telling the reason.

### Time table

The first participants started the intervention in April 2016, and the recruitment was completed in April 2018. Altogether 635 participants were recruited. The first participants finished the 3-year intervention in April 2019, and the last participants will finish it in September 2021. The last participants in the control group will have a 3-year visit in September 2021.

### Baseline data

The baseline characteristics of the participants in the intervention groups are presented in Table 2 (low and high genetic risk groups combined). The mean age of the participants was 65.0±5.9 years (mean ± SD) at the baseline, and they were obese with the mean waist circumference higher than recommended. Fasting plasma glucose concentration was within the range of IFG (5.6–6.9 mmol/l), 2-h glucose concentration <11.1 mmol/l, and HbA1c (<48 mmol/l or <6.5 %). Blood pressure and concentrations of total and LDL cholesterol were slightly higher than recommended.

**Table 2 T0002:** Baseline characteristics of the participants in the intervention group (*n* = 635)

Variables	Range	Mean ± SD
Age, years	51–75	65.0±5.9
Body mass index, kg/m^2^	25.0–48.5	28.7±3.2
Waist circumference, cm	84.0–149.0	103.3±9.0
Systolic blood pressure, mmHg	101–193	134±15
Diastolic blood pressure, mmHg	60–117	84±9
Fasting glucose, mmol/l	5.6–6.9	6.0±0.3
2-h glucose, mmol/l	2.7–10.9	6.3±1.6
HbA1c, mmol/mol	29–45	37.5±3.1
Total cholesterol, mmol/l	2.49–7.91	5.03±1.00
Low density lipoprotein-cholesterol, mmol/l	1.05–5.88	3.10±0.90
high density lipoprotein-cholesterol, mmol/l	0.60–2.80	1.38±0.36
Total triglycerides, mmol/l	0.46–5.73	1.37±0.67

## Discussion

Our study will be the first study to compare the effect of lifestyle intervention on the prevention of incident T2D and the worsening of hyperglycemia in people with high genetic risk of T2D compared with people with low genetic risk of T2D.

If the effects of the lifestyle intervention are independent from the genetic risk of the participants, the implications of our study will be of great importance for the entire T2D research community, health care providers, and individuals at high risk for T2D. In this case, lifestyle intervention is beneficial for all individuals at risk for developing T2D, independently of genetic risk. If the effects of lifestyle intervention depend on the genetic risk, then individualized intervention programs are needed based on the GRS in people at high risk for T2D.

Due to the high number of people at risk for T2D in most countries, it will be challenging to organize individualized lifestyle counseling. In our study, lifestyle counseling is group-based, and a special website designed for this study is used for nutritionists-participant and participant-nutritionists contacts. From the resources point of view, it is important to examine whether a group-based intervention is effective similarly to a personal lifestyle counselling, and this study is likely to give an answer to this important question.

There are several previous lifestyle intervention studies, in counseling which the efficacy of lifestyle intervention on the prevention of T2D has been reported. Most of these studies have been performed in participants with IGT. In the present study, participants with IFG with or without IGT have been included. Most of the studies have combined diet and physical exercise, and a minority of the studies have only dietary intervention (17). In the systematic review and meta-analysis, the risk ratio (RR) was 0.68 (95% CI 0.5; 0.84) for dietary interventions and 0.59 (0.51; 0.69) for interventions combining diet and physical activity (17). In a more recent SRMA, the RR was 0.53 (0.41; 0.67) for interventions combining diet and physical activity (18).

In previous studies, the interventions have mainly been individual based. In the Finnish DPS, the participants met clinical nutritionist seven times during the first year of the intervention and three times per year thereafter (4). In the DPP, the participants were contacted by phone (5). In real-world setting, a group-based approach has been studied. In an SRMA of real-world lifestyle modification aiming for T2D prevention, participants receiving group counseling by health care professionals had an RR of 0.67 (0.49; 0.92) as compared with control participants (19).

The most significant challenge of our study is that the group-based intervention utilizing a specific website is not efficient enough. However, due to an increasing number of people with impaired glucose metabolism or T2D, it is important to test this type of intervention since individual counseling is usually not possible, not at the present time and even less in the future, since the number of people at risk for T2D is increasing.

The results of the present study will reveal whether a lifestyle intervention (diet, physical activity, and weight maintenance/weight loss) is as effective in the prevention of incident T2D and the worsening of hyperglycemia in people with high number of T2D risk alleles compared with people with low number of T2D risk alleles, and whether a group-based intervention utilizing a website designed for this purpose is as effective as an individual-based intervention.

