Several diabetes prevention trials have been published on the effects of lifestyle changes (diet and physical activity), and a meta-analysis of these trials reported a 57% reduction in incident T2D (8). There are no previous trials investigating the effect of the genetic background of the participants (the number of the risk alleles for T2D) on the effect of the prevention of T2D. Therefore, the aim of the T2D-GENE trial is to investigate the effects of lifestyle intervention (diet, physical activity, and weight maintenance/weight loss) on the prevention of incident T2D and the worsening of hyperglycemia in people with a high number of T2D risk alleles compared with people with a low number of T2D risk alleles. The second aim of our study is to investigate whether a group-based intervention utilizing a website is as effective as is an individual-based intervention. The hypotheses of the study are that lifestyle intervention is efficient independent of the number of T2D risk alleles (high and low genetic risks of T2D), and that a group-based intervention is as effective as an individual-based intervention in the prevention of T2D.

The primary outcome of our study is incident T2D defined by fasting plasma glucose ≥7.0 mmol/l or 2-h glucose ≥11.1 mmol/l in an oral glucose tolerance test (OGTT) or HbA1c ≥ 47 mmol/mol (6.5%), according to the American Diabetes Association criteria (9), or drug treatment for T2D started during a 3-year intervention trial. The secondary outcomes are changes in glucose area under the curve (AUC) in an OGTT, changes in insulin secretion and insulin sensitivity, and incident cardiovascular disease (CVD) events (fatal or non-fatal myocardial infarction, fatal or non-fatal stroke, death from cardiovascular causes or incident heart failure).

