### Calculation of the sample size

The average proportion of participants in whom IGT progressed to T2D in the Finnish DPS study was 3%/year in the intervention group and 6%/year in the control group (4). The absolute incidence of T2D was 32 cases/1,000 person-years in the intervention group and 78/1,000 person-years in the control group (4). Using the results from the Finnish DPS study and assuming similar rates of incident T2D (6%/year) in the control group, a total of 69 individuals of 300 (our sample size) or 23% will develop diabetes during a 3-year intervention. The corresponding numbers in the intervention groups are 31 of 300 or 10%, indicating a 13% difference in incident T2D between these two groups. If α = 0.05 and β = 0.95, only 60 individuals/group are needed to demonstrate statistically significant difference between the intervention and control groups. Our group-based intervention might be less efficient than individual-based approach in the Finnish DPS study. If the effect of intervention is 6% (about half of the effect of that of the Finnish DPS study), then 267 participants are needed. Assuming around 10% of dropouts in this trial, a sample size of 300/each group has a power of 95% to demonstrate statistically significant reduction in incident T2D in the intervention groups compared with the control groups.

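### With 300 per cell the trial cannot support a conclusion that the intervention prevents type 2 diabetes equally well at high and low genetic risk, although the Discussion says the results will settle this

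*Protocol article*

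**What the plan says.** The introduction (the text under the ClinicalTrials.gov ID heading) hypothesises that "lifestyle intervention is efficient independent of the number of T2D risk alleles". The last paragraph of the Discussion says the results will establish whether the intervention "is as effective in the prevention of incident T2D and the worsening of hyperglycemia in people with high number of T2D risk alleles" as in people with a low number.

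The Abstract conclusion and the Discussion then set out two implications. If the effect is independent of genetic risk, the intervention benefits everyone at risk. The other branch is: "If the effects of lifestyle intervention depend on the genetic risk, then individualized intervention programs are needed".

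The only sizing statement, in Calculation of the sample size, is that 300 per group has 95% power to "demonstrate statistically significant reduction in incident T2D in the intervention groups compared with the control groups". Statistical analyses describes a Cox model with study group as covariate in the low and high genetic risk score (GRS) groups. The article gives no precision, power or acceptable difference for the comparison of the two effects.

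**The concern.** Saying that an effect is the same in two groups is a claim of equivalence. It needs an interval for the difference between the effects that is narrow compared with the benefit itself. A trial sized to show benefit over control is usually far too small for that, because the contrast between two effects carries the sampling error of four cells.

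Two results could be mistaken for sameness: a non-significant difference between the GRS groups, or a significant benefit in both. Neither shows it. At stake is the article's main practical message, that one programme suits everyone whatever their genetic risk. It could be published on data that are also compatible with one group getting half the benefit or less.

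**Working it through.** **The plan's own figures.** None is given for high against low GRS. For intervention against control the article says "If α = 0.05 and β = 0.95, only 60 individuals/group are needed" (β = 0.95 is read here as power), and 267 for a 6-point effect. Using n = (1.96 + 1.645)² × [p₁(1−p₁) + p₂(1−p₂)] / (p₁−p₂)²:
- 23% against 10%: 12.996 × 0.2671 / 0.0169, about 206 per group, not 60.
- 23% against 17%: 12.996 × 0.3182 / 0.0036, about 1,149, not 267. The pairs 18/12 and 16/10 give about 914 and 811.

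These figures do not reproduce. That is a separate matter, but it means the sizing section lends no hidden reserve to the harder question below.

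**Inputs.**
- Four cells of 300 (Abstract, Methods).
- Control risk: "a total of 69 individuals of 300 (our sample size) or 23% will develop diabetes during a 3-year intervention".
- Intervention risk: "31 of 300 or 10%, indicating a 13% difference in incident T2D between these two groups".
- A 6-point effect if the group programme is weaker. The pair of risks is not stated; 23% against 17% (69 and 51 events) is assumed, with other pairs below.
- 10% dropout leaves 270 per cell.
- Equal risks and equal true effects in both GRS groups unless stated, and two-sided 5%.

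**Formulas.** HR = ln(1−p_int) / ln(1−p_con). SE of the log ratio of HRs = √(sum of 1/events over four cells). The 95% factor is exp(1.96 × SE). The smallest margin met with 80% power when the effects are identical is exp[(1.96 + 0.842) × SE] in one direction, or exp[(1.645 + 1.282) × SE] for two one-sided tests (TOST, the 90% interval rule).

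**6-point effect (69 and 51 events).**
- HR 0.713; losing the whole benefit is a 1/0.713 = 1.40-fold ratio.
- SE = √[2(1/69 + 1/51)] = 0.261; 95% factor 1.67 (1.72 at 270 per cell).
- TOST with a margin as wide as the whole benefit cannot succeed: the 90% half-width is 1.645 × 0.261 = 0.430, against ln 1.40 = 0.338.
- The other pairs agree: 18/12 gives a factor of 1.82 against 1.55, and 16/10 gives 1.91 against 1.66.

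**13-point effect (69 and 31 events).**
- HR 0.417; whole benefit 2.40-fold.
- SE = √[2(1/69 + 1/31)] = 0.306; 95% factor 1.82 (1.88 at 270).
- 80%-power margin: 2.36 in one direction, 2.45 by TOST.
- Retaining half the log-HR benefit means a margin of √2.40 = 1.55, or 0.437 on the log scale. The 90% half-width is 0.503, so TOST cannot succeed even with an observed ratio of exactly 1. One-directional power is Φ(0.437/0.306 − 1.96), about 30%.

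**Risk-difference scale.** The half-width is 1.96 × √{2[p_c(1−p_c) + p_i(1−p_i)]/300}. This gives 9.0 points (23/17), 8.0 (18/12) or 7.6 (16/10) against a 6-point benefit, and 8.3 points (23/10) against 13. The one-directional 80%-power margin under 23/10 is 11.8 points.

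**Unequal effects.** With 13 points in one group and 6 in the other, the log ratio is ln(0.713/0.417) = 0.536. SE = √(1/69 + 1/31 + 1/69 + 1/51) = 0.284, so the mean z is 1.88. The chance of non-significance at 5% is 53% (57% at 270 per cell). With no benefit at all in one group, the same test misses it 11% of the time (15% at 270).

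**Lower event rate.** Taking 6% a year at face value gives 1 − exp(−0.18) = 16.5%, or 49.5 control events. With the same ratio of events (22.2), SE = 0.361 and the 95% factor is 2.03.

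**The case against.** Three stronger readings are tempting, and the documents do not support them.

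- *The design can only exclude differences larger than the whole expected benefit.* This holds for the 6-point effect. It does not hold in general for 13 points: the interval factor of 1.82 is well inside 2.40, the one-directional margin of 2.36 is just below it, and 11.8 points is below 13. Only the TOST margin of 2.45 exceeds it, and with 317.5 per cell (635 recruited, assuming an even split and controls to match) that falls to 2.39.
- *The authors will read a non-significant difference as independence.* The text is conditional: it says what would follow if the effect were independent, or if it were not. No test or decision rule is stated. The 53% describes a test the article does not contain, and it drops to 51% at 317.5 per cell.
- *The missing margin is itself the defect.* A margin and the handling of an inconclusive result could sit in an analysis plan that is not shown.

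There is also a milder reading of the hypothesis: the intervention works in each GRS group. It fits the within-group Cox model and the intervention-against-control sizing. It does not fit the closing paragraph of the Discussion, which compares effectiveness between the groups.

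What remains is that no analysis plan can alter 300 per cell, and the published promise depends on that number.

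**Conclusion.** The point holds in a limited form. The article promises an answer on equal effectiveness against incident diabetes that the stated cell size cannot give. Under the 6-point effect the interval for the ratio of effects is wider than the whole benefit, for every pair of risks tried and on both scales. Under the 13-point effect the trial could exclude little more than complete loss of benefit, and TOST could not show that half is retained. A real two-to-one difference in absolute benefit would go undetected about half the time.

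This rests on equal risks in the two GRS groups (apart from the unequal-effects case), two-sided 5%, and the article's own 3-year risks. Dropout or a lower control risk widens the intervals; the 635 recruited narrows them only slightly. Precision for the continuous glycaemia outcomes, which the same sentence of the Discussion also covers, was not assessed.

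**What to change.** In the Abstract conclusion and the Discussion:

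1. Say that the trial estimates the high-to-low GRS ratio of hazard ratios with its 95% confidence interval, expected to be about the estimate times or divided by 1.7 to 1.8 at 300 per cell, and wider with dropout or fewer events.
2. Add a third outcome, not resolved, beside independent and dependent.
3. State that neither a non-significant difference nor significance in both GRS groups will be reported as independence of genetic risk.
4. State that the claim the trial was sized for is benefit of intervention over control within each GRS group. The power attached to that claim needs its own correction.

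If a margin for calling the effect independent is wanted, fix it before GRS unblinding and acknowledge that a half-benefit margin is out of reach at the planned event counts. With the 13-point effect on the risk-difference scale, excluding loss of half the benefit (6.5 points) with 80% power would take about 993 per cell in one direction, or 1,083 by TOST.

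The cost is wording only, with no extra participants or visits. The downside is a weaker promise, since the likely report is that the question is not resolved.

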## Data Availability

Not applicable at this point (protocol article).
